## Abstract

**Background:**

Diabetes mellitus is a major risk factor for prolonged hospital stays, renal failure, and mortality in patients having coronary artery bypass grafting (CABG). Complications pose a serious threat to patients and prolong intensive care and hospital stays. Low glomerular filtration rate (GFR) due to existing renal impairment or volume depletion may exacerbate acute renal impairment/failure in these patients. Preoperative volume replacement therapy (VRT) is reported to increase the GFR and we hypothesize that VRT will reduce renal impairment and related complications in diabetic patients.

**Objective:**

The objective of this study is to establish the efficacy of preoperative VRT in reducing postoperative complications in diabetic patients undergoing CABG surgery. Time to “fit for discharge”, incidence of postoperative renal failure, cardiac injury, inflammation, and other health outcomes will be investigated.

**Methods:**

In this open parallel group randomized controlled trial, 170 diabetic patients undergoing elective or urgent CABG surgery received 1 mL/kg/hour of Hartmann’s solution for 12 consecutive hours prior to surgery, versus routine care. The primary outcome was time until participants were “fit for discharge”, which is defined as presence of: normal temperature, pulse, and respiration; normal oxygen saturation on air; normal bowel function; and physical mobility. Secondary outcomes included: incidence of renal failure; markers of renal function, inflammation, and cardiac damage; operative morbidity; intensive care stay; patient-assessed outcome, including the Coronary Revascularization Outcome Questionnaire; and use of hospital resources.

**Results:**

Recruitment started in July 2010. Enrolment for the study was completed in July 2014. Data analysis commenced in December 2016. Study results will be submitted for publication in the summer of 2017.

**Conclusions:**

VRT is a relatively easy treatment to administer in patients undergoing surgical procedures who are at risk of renal failure. This experimental protocol will increase scientific and clinical knowledge of VRT in diabetic patients undergoing elective or urgent CABG surgery. Findings supporting the efficacy of this intervention could easily be implemented in the health care system.

**Trial Registration:**

International Standard Randomized Controlled Trial Number (ISRCTN): 02159606; http://www.controlled-trials.com/ISRCTN02159606 (Archived by WebCite at http://www.webcitation.org/6rDkSSkkK)

## Introduction

Diabetes mellitus (DM) has been recognized as a major risk factor for atherosclerosis [1,2], and its prevalence is on the rise due to an increasingly aging and obese population [3]. DM is also a major risk factor for postoperative renal failure, infections, and in-hospital and late mortality in patients undergoing coronary artery bypass grafting (CABG) surgery [4,5]. Diabetic patients currently represent approximately 20% of all patients undergoing CABG surgery [3,4,6-8]. This rate does not include undiagnosed DM, which has been reported to be 5.2% of all patients admitted for CABG [6]. In keeping with the United Kingdom (UK) average, approximately 20% of CABG patients have a diagnosis of DM on admission at our institution [4]. However, we have previously demonstrated that only 40% of patients experiencing postoperative moderate-to-poor blood sugar control after CABG were diagnosed as having DM prior to surgery [9]. This finding suggests that the prevalence of undiagnosed DM in patients admitted for CABG may be grossly underestimated, and emphasizes the importance of optimizing the perioperative management of these patients.

Renal insufficiency and acute kidney injury (AKI) remain frequent and serious complications following cardiac surgery, and are associated with other postoperative complications, mortality, prolonged hospital stays, and costs [7-9]. AKI following CABG is also consistently associated with DM [7-9]. Our group has demonstrated that DM is an independent predictor of renal insufficiency in a large cohort study [9], consistent with previous reports linking DM with AKI [8]. AKI can be defined in various ways. The introduction of the Risk, Injury, Failure, Loss, and End stage (RIFLE) criteria have standardized the National Health Service (NHS) definition of AKI and allowed more objective comparisons between different studies [10]. In its most severe form, AKI requires dialysis [10-12]. Death is 7-8 times more frequent in patients requiring dialysis because of AKI [13], but less severe renal dysfunction is also strongly associated with mortality [14]. AKI is reported to be more common after CABG in diabetic patients compared to nondiabetic patients [6,9].

Body fluid volume depletion may also be prevalent in patients undergoing CABG, especially diabetics. One factor leading to volume depletion is preoperative use of diuretics, which can cause hypovolemia, which reduces cardiac preload, cardiac output, and related organ perfusion. In addition, the use of vasodilators can also lead to relative volume depletion and hypotension [15]. Diminished renal perfusion can be a consequence of volume depletion, and of hemodynamic changes associated hypovolemia or with impaired left ventricular function [15,16]. In addition, agents such as nonsteroidal antiinflammatory drugs, cyclosporine, angiotensin-converting enzyme inhibitors, and angiotensin II receptor blockers can decrease renal perfusion [17-19]. In these situations, the resultant diminution in renal blood flow and estimated glomerular filtration rate (eGFR) can lead to postoperative renal insufficiency, and surgical patients could benefit from mild preoperative fluid replacement therapy since this has been associated with an increase in GFR [20]. A reduced eGFR may simply be a reflection of ongoing baseline renal impairment, which is also typical of diabetic patients.

Isotonic crystalloid solutions, such as Hartmann’s solution, are the first choice for volume replacement therapy (VRT) [21]. Unlike plasma expanders, crystalloid solutions have no nephrotoxic (or other specific) side-effects [21]. Isotonic crystalloid solutions are distributed rapidly into the tissue interstitial compartment and have a half-life of 20-30 minutes in the intravascular space.

This study protocol seeks to examine the effects of preoperative gentle VRT on postoperative time to “fitness for discharge”, renal failure, inflammation, cardiac injury, postoperative complications, and mortality in diabetic patients undergoing CABG surgery. A definitive trial of VRT in this indication is required before this relatively easy-to-administer treatment can be proposed as adjuvant therapy in diabetic patients undergoing cardiac surgery, or indeed other major surgical procedures. We hypothesize that the postoperative incidence of renal failure will be lower, and postoperative recovery faster, in diabetic patients treated with gentle VRT prior to surgery.

The main objective of the Volume Replacement in Diabetic Patients Undergoing Coronary Artery Bypass Grafting Surgery: Protocol for a Randomized Controlled Trial (VeRDiCT) is to evaluate the effect of VRT versus routine care on time until participants are “fit for discharge”, which is defined as normal temperature, pulse, respiratory rate, oxygen saturation on air, bowel function, and physical mobility. Secondary objectives will be to evaluate the effect of VRT versus routine care on the incidence of: postoperative renal failure and biochemical serial markers of renal function, inflammation, and cardiac damage; operative morbidity; intensive care stay; and use of hospital resources. In addition, we will evaluate patient-assessed outcome, which will be based on the serial administration of the Coronary Revascularization Outcome Questionnaire (CROQ).

We are conducting an open, parallel group, randomized controlled trial (RCT) in which diabetic elective or urgent patients undergoing CABG surgery will receive VRT or routine care. This treatment has already been shown to prevent AKI in certain clinical scenarios [21]. The most likely mechanism of action of VRT is by increasing eGFR [20]. It has also been suggested that VRT is essential to obtain adequate systemic circulation and microcirculation [22].

## Methods

### Type of Clinical Trial

This is an open, parallel group, RCT of preoperative VRT with Hartmann’s solution versus routine care in diabetic patients undergoing CABG. The trial is not blinded, as it is not possible to mask the infusion of the Hartmann’s solution. A covered drip could have been set up for all trial patients but it would still be obvious to the patient and those responsible for their care whether or not a fluid infusion was being given.

### Study Setting

This study was conducted in Bristol, UK at the Bristol Heart Institute, University Hospital Bristol NHS Foundation Trust. A parallel study was run at Rabindranath Tagore International Institute of Cardiac Sciences (RTIICS), Kolkata, India. The results of both trials are being combined and recruitment at both sites has contributed to the target sample size. RTIICS was responsible for research governance and approvals of their study.

### Ethical Review

The University Hospital Bristol NHS Foundation Trust has sponsored the trial in the UK. The trial was approved by the North Somerset & South Bristol Research Ethics Committee (REC; reference 10/H0106/1) in February 2010 in the UK. The study is a Clinical Trial of an Investigational Medicinal Product (IMP) and was approved by the UK Medicines and Healthcare Products Regulatory Agency (MHRA) in 2010. The study is registered (ISRCTN 02159606).

### Participants

For this study, 170 diabetic patients undergoing CABG surgery were recruited to the two parallel studies according to the flow chart shown in Figure 1.

**Figure 1 figure1:**
[figure not shown]
Study flow chart.

### Participant Recruitment

To assess eligibility, a member of the local research team (study clinician/research nurse/trial coordinator) in collaboration with the chief investigator (CI) has assessed patients’ medical notes to assess eligibility. VRT can be used in most adult diabetic patients for whom CABG is planned. Therefore, all diabetic adults aged >16 years and <80 years having elective or urgent isolated CABG for the first time represented the target study population. Participants could enter the study if all of the following applied: (1) patient was diagnosed with type I or type II diabetes, treated with oral medication and/or insulin (ie, not diet controlled only); (2) aged >16 and <80 years; (3) underwent elective or urgent isolated first-time CABG; (4) left ventricular ejection fraction >30%. Participants were excluded from the study if they had: (1) undergone previous cardiac surgery; (2) emergency or salvage operation; (3) chronic renal failure requiring dialysis; (4) current congestive heart failure; (5) left ventricular ejection fraction <30%.

### Information and Consent

Potential trial participants were identified from CABG waiting lists (elective patients) and theatre schedules (urgent patients). All potential participants were sent or given an invitation letter and Patient Information Sheet (PIS) approved by the REC, which described the study. The patient was given time to read the PIS and to discuss their participation with others outside the research team (eg, relatives or friends) if they wished. Most patients had at least 24 hours to consider whether they would participate. In a few cases this time interval was shorter (eg, for patients admitted for urgent surgery without prior notification to the waiting list coordinator). Details of all patients approached for the trial and reason(s) for nonparticipation (eg, reason for being ineligible or patient refusal) were documented. Signed informed consent was required and taken from all eligible patients who were willing to participate.

### Study Medication

Hartmann’s solution is classed as an IMP and is therefore under the regulation of the MHRA. The IMP was only administered to patients randomized to the VRT arm (there was no placebo). The dosage of the solution is dependent on body mass as follows: 1mL/kg/hour for 12 hours; therefore, maximum dose (mL) = body mass x 12.

Study medication was stored at room temperature in a temperature-monitored lockable cupboard. If the surgery was delayed and rescheduled to take place the next calendar day (morning or afternoon slot), the intervention was not to be repeated. If the surgery was delayed for 2 days or more, the intervention was repeated, and the IMP was represcribed.

### Procedure

Patients were randomly assigned in a 1:1 ratio using an Internet-based randomization system (Sealed Envelope Ltd). Cohort minimization was used to achieve balance between groups. Random allocations were generated by computer once the relevant baseline data required to identify the patient and establish eligibility were entered into the system. Consented patients were randomized in the evening on the day of admission, with the VRT intervention delivered overnight prior to surgery. If the operation was unexpectedly rescheduled, the patient retained their study number and randomized allocation. There was no requirement to have code breaking procedures in place. The trial was unblinded and the treatment was recorded in the medical notes and on the fluid chart.

Participants were randomly assigned to receive either VRT (1 mL/kg/hour of Hartmann’s solution for 12 consecutive hours prior to surgery) or usual care (no additional preoperative fluids). Both groups were fasted for 6 hours prior to surgery. At surgery, patients were managed according to routine anesthetic, surgical, and perfusion standards. Undertaking of coronary surgery with or without cardiopulmonary bypass and cardioplegic arrest were performed according to the surgeon’s preference. All other aspects of the patient’s preoperative and postoperative management were in accordance with existing protocols in use. The VRT was the only intervention administered over and above the usual care. Participants were asked to donate small blood and urine samples before, during, and after surgery, as well as any leftover tissue available during surgery that would normally be discarded. At discharge, participants were asked to indicate how they felt about their readiness to go home. At 6-8 weeks postsurgery, participants were asked to complete a telephone assessment of their wounds to ascertain presence of infection and answer a question regarding readmissions. Wounds were assessed using a recognized quantitative scoring method that provides a numerical score related to the severity of wound infection using objective criteria, including additional treatment, serous discharge, erythema, purulent exudate, separation of the deep tissues, isolation of bacteria, and the duration of inpatient stay (ASEPSIS). Three months after surgery, participants were asked to complete the CROQ. Key data collection points are shown in Table 1.

**Table 1 table1:** Key data collection points of measured outcomes.

	Pre-surgery	Day of surgery	Day 1	Day 2	Day 3	Day 4	Day 5	Discharge	6-8 weeks	3 months
Eligibility	✓									
Written consent	✓									
Randomized allocation	✓									
Demographics and past medical history	✓									
Blood for serum creatinine (AKI/ eGFR) and other biochemical predictors of health outcome	✓	✓ ✓ (0, 12 hours)	✓ ✓ (24, 36 hours)	✓	✓	✓	✓			
Operative details		✓								
Clinical outcomes								✓		
CROQ	✓									✓
Readiness for discharge								✓		
ASEPSIS wound inspection					✓		✓	✓		
ASEPSIS post-discharge surveillance									✓	
Resource use data								✓	✓	✓
Urine sample (renal glomerular and tubular injury, microRNA and other biochemical predictors of health outcome)	✓	✓	✓	✓			✓			
Blood for fasting glucose and hemoglobin A1c	✓ (prior to chest opening)									
Blood for serum and plasma microRNA	✓	✓	✓				✓			
Leftover material/specimens collected during surgery		✓ (intra-operatively)								
Blood for Troponin T	✓	✓ ✓ (0, 12 hours)	✓	✓	✓		✓			
Blood for C-reactive protein	✓	✓ ✓ (0, 12 hours)	✓	✓	✓		✓			

## Results

### Primary Outcome

The primary outcome is the time until patients are classified as “fit for discharge”, since prevention of renal impairment by the proposed intervention is expected to impact the risk of many postoperative complications. A patient must have normal temperature, pulse, respiratory rate, oxygen saturation on air, and bowel function and be physically mobile (taking into account preoperative mobility such as wheel chair use) in order to be classified as “fit for discharge”.

### Secondary Outcomes

Secondary outcome measures include: (1) measurements of serum creatinine from blood samples collected preoperatively and postoperatively; (2) microalbumin/creatinine ratio measured in urine samples collected preoperatively and postoperatively; (3) N-acetyl-beta-D-glucosaminidase release measured in urine samples collected preoperatively and postoperatively; (4) participants’ judgement about readiness for discharge; (5) in-hospital mortality and morbidity; (6) use of health care resources; (7) health-related quality of life as measured by the CROQ; (8) preoperative fasting blood glucose; (9) micro-ribonucleic acid (RNA) measured in preoperative and postoperative urine, serum, and plasma samples; (10) C-reactive protein (CRP) measured preoperatively and postoperatively; and (11) serial troponin T release measured preoperatively and postoperatively. Measures 8-11 were only included in a subgroup of the UK trial.

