#### Reporting of Adverse Events

Adverse events were recorded from the randomization time point, throughout the duration of the participant’s postoperative hospital stay, and for the predefined 3-month follow-up period. Any adverse event spontaneously reported by the participant, or observed by the researcher or the research team, was be recorded on the case report form (CRF) that was designed for this purpose. Events were also reported in accordance with the International Conference for Harmonization of Good Clinical Practice guidelines and followed the sponsor’s policy for safety reporting. Expected events included those related to administering Hartmann’s solution, as well as complications associated with cardiac surgery.

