### Data Analysis

#### Sample Size

There were no previous trials of VRT in diabetics, hence no data to guide the likely target difference in renal function to be observed for the purpose of sample size calculation. No published data existed for the primary outcome of “fit for discharge” (chosen to minimize biases that can affect standard data on postoperative length of stay) and the sample size calculation described here uses information about actual postoperative length of stay as a proxy for the primary outcome. The median postoperative stay for diabetic patients having CABG (from our institutional database) is 7 days. Assuming time to “fit for discharge” is shorter than actual stay, we have proposed that the trial should be able to detect a 25% difference in the proportion of patients “fit for discharge” at 6 days between VRT and usual care groups (ie, 75% vs 50%). We have proposed that 170 participants would be required to detect this target difference with 90% power and 5% significance (2-tailed).

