#### Statistical Analyses

Time to “fit for discharge” and length of Intensive Care Unit and postoperative hospital stays will be analyzed as time-to-event data using regression modelling for survival data. Means for continuous outcomes (transformed logarithmically if required) will be compared using regression modelling, adjusting for baseline covariates where available; “mixed models” will be used for outcomes with repeated measures such as eGFR and markers of glomerular, tubular, renal function, microRNA, CRP, and troponin T. Findings will be reported as effect sizes with 95% confidence intervals. The frequencies of complications and conversions will be tabulated descriptively. Analyses will be based on the intention-to-treat (as treated compared to intention-to-treat); conversions are expected to be rare.

A subgroup analysis comparing trial-specific (eg, UK or India) primary and secondary biochemical marker outcomes is prespecified in the statistical analysis plan. Subgroups will be compared by adding an allocation by trial interaction term into the model.

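### The listed mortality and morbidity outcome stops counting at discharge, which VRT is meant to bring forward, so the descriptive comparison may favour VRT without any true effect

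*Protocol article*

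**What the plan says.** In the protocol article, Secondary Outcomes lists "in-hospital mortality and morbidity" as item 5. Table 1 (under Procedure) agrees: the row "Clinical outcomes" is ticked in the Discharge column and nowhere else.

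The Introduction hypothesises less renal failure and "postoperative recovery faster, in diabetic patients treated with gentle VRT prior to surgery". The primary outcome is time to fitness for discharge. Under Statistical Analyses, ICU and "postoperative hospital stays will be analyzed as time-to-event data", so length of stay is itself compared between arms. The same section says that complication frequencies will only be tabulated descriptively.

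Other data run past discharge:
- Adverse events are recorded from randomization, through the hospital stay, "and for the predefined 3-month follow-up period". Complications of cardiac surgery are among the expected events (Reporting of Adverse Events).
- At 6-8 weeks participants have a telephone wound assessment and "answer a question regarding readmissions" (Procedure). Table 1 shows this contact as "ASEPSIS post-discharge surveillance".
- Resource use is collected at discharge, 6-8 weeks and 3 months (Table 1).

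**The concern.** The observation window of outcome 5 closes at an event that the treatment is designed to bring forward. If VRT patients go home earlier, complications that would have been counted in hospital under usual care happen at home and drop out of the VRT count. The two arms are then compared over unequal times, and the inequality favours VRT.

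The abstract states the trial's objective as efficacy in reducing postoperative complications, so readers will take the complication table as evidence for that objective although no test is attached. When a trial succeeds by making patients ready for home sooner, the natural question is whether complications fell or only moved to after discharge. A count that ends at discharge cannot answer it.

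**Working it through.** **1. The plan's own figure.** Sample Size gives 75% v 50% fit for discharge at day 6, 90% power, two-sided 5%, 170 participants. The two-proportion formula with continuity correction gives 85 per arm, or 170 in total, so the figure reproduces (77 per arm, 154 in total, without the correction). The sample size is not in dispute.

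**2. Size of the planned effect as a hazard ratio.** Under proportional hazards, 50% v 25% not yet fit at day 6 gives HR = ln 0.25 / ln 0.50 = 2.0. A smaller effect is used as a second case. If all 170 participants have the event, the HR detectable with 90% power is exp(2 × 3.2415 / √170) = 1.64.

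**3. Inputs for the window effect.**
- From the article: median postoperative stay of 7 days (Sample Size).
- Assumed: the stay distribution is Weibull with shape 3; the HR on fitness carries over in full to actual discharge; complications are independent of stay; VRT has no true effect on complications.
- Assumed, because the article gives no complication rates or timing: the complication hazard h(t) is constant per day, or decays as exp(−t/τ) with τ = 5 or 3 days.

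**4. Formula.** The probability of still being in hospital at day t is S(t) = exp(−HR × ln 2 × (t/7)³), with HR = 1 for usual care. The expected in-hospital count per patient is proportional to ∫ h(t) S(t) dt. The VRT/usual-care ratio of this integral is the artefact; a fixed window gives 1.00.

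With a constant hazard the ratio has a closed form, HR^(−1/3): 2.0^(−1/3) = 0.79 and 1.64^(−1/3) = 0.85. The other cases were integrated numerically.

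| Complication timing | HR 2.0 (median stay 5.6 days) | HR 1.64 (median stay 5.9 days) |
|---|---|---|
| Constant daily hazard | 0.79 (21% fewer) | 0.85 (15% fewer) |
| Decaying, τ = 5 days | 0.89 (11% fewer) | 0.92 (8% fewer) |
| Decaying, τ = 3 days | 0.93 (7% fewer) | 0.95 (5% fewer) |

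**5. Sensitivity to the stay curve.** A second set of curves was fixed at 50% and 25% remaining at day 6, with Weibull shape 1 to 3, minimum stay 0 or 3 days, and event timing from a 3-day mean to uniform over 30 days. With a 3-day minimum stay the ratio runs from 0.97 down to 0.70. The extreme case, an exponential stay with no minimum and events spread over 30 days, gives 0.52. The direction is the same throughout; the size is not.

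**6. In patients.** Assume 10 to 30% of 85 patients per arm have a complication, that is 8.5 to 25.5 patients. A 5 to 11% fall is then 0.4 (8.5 × 0.05) to 2.8 (25.5 × 0.11) patients. A 21% fall is 1.8 to 5.4 patients.

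**The case against.** A reader might infer that this trial ignores or hides what happens after discharge. The article does not support that. Adverse events, with surgical complications named among the expected ones, are recorded to 3 months in both arms, wounds and readmissions are asked about at 6-8 weeks, and resource use runs to 3 months. The in-hospital limit belongs to outcome 5, not to data capture.

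A reader might also infer that the trial is set up to claim fewer complications as an artefact. No test of complications is planned, only a descriptive table, and the primary analysis is untouched. Serum creatinine, the marker closest to the renal hypothesis, is sampled on scheduled days to Day 5 rather than as an open count to discharge. That wound score and readmission are not named in the outcome list is ordinary condensation in an article and is not part of this point.

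The size is open to challenge too. Fitness for discharge is not discharge, and the article itself separates the two. Fitness requires normal temperature, pulse, respiration, oxygen saturation and bowel function, so a patient with a complication under way will often stay in hospital and be counted. That shrinks the artefact below a model that treats stay and complications as independent. The protocol also expects VRT to shorten stay partly by preventing complications, so an effect on stay with none on complications is a deliberate null case, not a forecast.

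These points reduce the size and limit the consequence. They do not make the window equal: if actual stay shortens, outcome 5 as worded still compares different observation times.

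**Conclusion.** The point holds as one of interpretation. Outcome 5 has a window that depends on treatment, and if VRT shortens actual stay the descriptive comparison leans towards VRT with no true effect on complications. On the main stay curve the counted events fall by roughly 5 to 11% when complications cluster early and by up to about 21% with a constant daily hazard; other stay shapes widen this. All these figures assume that stay follows fitness in full and is independent of complications, and that event timing, which the article does not give, lies in the range shown. If VRT does not shorten actual stay, there is no such artefact. The sample size, the primary analysis and every planned test are unaffected.

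**What to change.** Make the mortality and morbidity comparison death and complications from randomization or surgery to the existing 3-month follow-up, taken from the adverse-event records and over the same period in both arms. Show readmission and wound infection to the 6-8 week contact alongside. Keep the in-hospital counts as supportive, labelled as depending on length of stay.

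Record when the change was made. Enrolment was completed in July 2014 and data analysis began in December 2016 (abstract, Results), so a change after that start should be labelled post hoc, especially in an open trial.

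No new data collection is needed; the work lies in the outcome definition, the tables and the record of the change. The downside is that events after discharge rest on adverse events reported spontaneously or observed by the team and on one telephone call about wounds and readmissions, so capture is less complete than in hospital. Showing both tables lets a reader weigh complete capture over unequal windows against less complete capture over equal ones.
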